The generalisability of the intervention will be based on collaboration with the Délégués de l'Assurance Maladie (DAM), who are already working on this issue on an operational and regular basis throughout France [42]. The DAMs, who are based throughout the country, make regular visits to GPs and promote good practice [43]. As this method of visiting GPs is original on an international scale, it is vital to demonstrate its impact on practices.

**The aim of the research** is to evaluate the effect of multifaceted interventions on GP prescribing by comparing the volumes of antibiotics dispensed at the end of 12 months of follow-up in a study comparing :

i) an intervention carried out by the Délégués d'Assurance Maladie (health insurance representatives) in general practices, combining a usual visit (with awareness-raising on antibiotic resistance, work on preconceived ideas, feedback on practices) and a demonstration of the use of Antibioclic (arm 1),

ii) an intervention carried out in the same way by Health Insurance delegates but without demonstration of Antibioclic (arm 2),

iii) compared with usual practice (arm 3).

1. **ORIGINALITY AND INNOVATION**

The project proposes an original study based on collaboration between various primary care players: a university team of general practitioners, regional health insurance teams in Pays de la Loire, a university hospital infectiology team, the MedQual centre (Antibiotic Resource Centre for the Pays de la Loire region) and the Antibioclic Clinical Decision Support System team.

The project was co-constructed with the Pays de la Loire health insurance scheme.

The originality of the intervention lies in the approach combining the strengths of tools that already exist and are established, but which act without synergy, despite their strong potential added value: face-to-face interventions by Assurance Maladie delegates in doctors' surgeries, support materials (enabling feedback on practices) built from prescription data collected by Assurance Maladie, and the Antibioclic internet tool to help with prescribing.

The robust design of a randomised study in 3 parallel arms covering the entire population of GPs in an administrative region will enable us to conclude both on the effect of a specific intervention by health insurance delegates in the form of the usual visits implemented by the social security system, and on the specific added value of demonstrating the use of Antibioclic.

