The demographic characteristics (age, sex) of the doctors and their mode of practice (type of commune of practice based on INSEE urban area zoning, "major centres" (codes 111, 112, 120), "small centres" (codes 211, 212, 221, 222), "isolated towns" (code 400), and "other communes" (code 300) [46]), group practice/independent practice, number of procedures/year, number of patients declared as attending physician) will be evaluated as factors potentially associated with the volume of antibiotics dispensed at the end of 12 months of follow-up.

5/ Compare the efficiency of drug dispensing after 12 months of follow-up.

- - 1. ***Secondary evaluation criteria***

The secondary evaluation criteria will be as follows:

1/ Overall volume of antibiotics dispensed at the end of 3 months' follow-up, measured in DDD per participating doctor.

Overall monthly volume of antibiotics dispensed, measured in DDD per participating doctor.

2/ Volume of broad-spectrum antibiotics most frequently responsible for antibiotic resistance in primary care (3rd generation cephalosporins, fluoroquinolones, amoxicillin/clavulanic acid) dispensed, measured in DDD per participating doctor.

3/ Sub-group analyses :

. Volume of antibiotics dispensed to patients over 65 (sub-group 1), measured in DDDs per participating doctor,

. Volume of antibiotics dispensed to children under 6 (sub-group 2), measured in DDD per participating doctor.

4/ Analysis of physician factors associated with the overall dispensing of antibiotics: age, sex, type of practice municipality [46], group practice/independent practice, number of procedures performed during the 12 months of follow-up, total number of patients declared in the attending physician's patient base.

5/ Cost-effectiveness analysis :

Incremental cost-effectiveness ratio comparing the 3 alternatives: i) DAM visit with Antibioclic demonstration, ii) DAM visit without Antibioclic demonstration, iii) usual practice.

1. **STUDY POPULATION**
   1. ***Description of the population***

The study covers the 5 departments of the Pays de la Loire region.

All GPs practising in the region who have seen more than 100 different patients in the year preceding the evaluation will potentially be eligible. The list of eligible GPs in the 5 departments will be established through a partnership with the Assurance Maladie, as in a previous study conducted by our team [47]. A preliminary study will enable us to anticipate the inclusion of more than 2,400 doctors.

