. Details of the resources consumed in each arm (averages and dispersion) and the average costs and efficiency per doctor will be calculated for each arm.

. A table will show the difference between the two groups in terms of costs and effectiveness, and the cost-effectiveness ratio will be calculated.

. As costs are not generally distributed according to a normal distribution, the incremental cost-effectiveness ratio and its confidence interval will be estimated using the non-parametric bootstrap method [49].

Finally, the probability that the use of antibioclic associated with a specific DAM visit is cost-effective compared with *a standard DAM visit* will be calculated for different values of willingness to pay for a reduction in antibiotics.

- - 1. ***STATISTICAL JUSTIFICATION FOR THE NUMBER OF INCLUSIONS***

After preliminary work to explore feasibility with the Assurance Maladie teams, the number of eligible doctors was estimated at 2,400 GPs who saw more than 100 different patients in 2018. The average number of DDDs dispensed per doctor in 2018 was 7,671, with a standard deviation of 5,360. In 2018, the average number of DDDs dispensed per doctor was 7671, with a standard deviation of 5360. Due to cluster randomisation, an inflation factor must be applied to calculate the number of subjects. In a previous study in the Loire Atlantique and Vendée regions [47], the average number of GPs per practice was 1.9. We set an intra-class correlation coefficient of 0.05 [50].

With an alpha risk of 5% and power of 80%, we can then demonstrate a significant difference if we have at least an average difference of 450 DDD per doctor (over the 12 months following the DAM visit) between the arms being compared.

- 1. ***Expected degree of statistical significance***

The alpha risk is set at 5%.

- 1. ***Method for taking into account missing, unused or invalid data***

All analyses will be performed on an intention-to-treat (ITT) basis.

The volumes of systemic antibiotics dispensed attributed to doctors who ceased their activity (end of career, moving outside the region, death, etc.) during the study follow-up period will be replaced by multiple imputation. A sensitivity analysis of the per-protocol population will also be carried out, excluding these doctors, as well as those who did not receive a visit from the DAM, and those who were not computerised.

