Given that two strategies will be compared with current practice, it may be necessary to estimate several incremental cost-effectiveness ratios (ICERs). A dominance analysis will be carried out to check whether certain interventions are dominated, i.e. more costly and less effective than another intervention. The average incremental cost-effectiveness ratio will be presented, together with its 95% confidence interval.

Univariate and multivariate sensitivity analyses will be carried out to check the robustness of the results to changes in assumptions about certain study parameters.

- 1. ***HEALTHCARE CONSUMPTION AND VALUATION***

The costs of the three strategies compared will be estimated in three stages [48]:

. collection of resources consumed,

. the unit monetary value of resources,

. estimated total costs.

Deliveries and costs of systemic antibiotics will be estimated using information retrieved from SNDS databases extracted by the Assurance Maladie in Pays de la Loire. The resources consumed will be valued at Assurance Maladie prices for drugs.

The resources used as part of the study will include :

. the costs associated with preparing and holding the training course,

. training time for DAMs,

. the development of communication material,

- the time it takes to create a digital visual aid,

- time for role-playing,

- the time it takes to write a sales pitch,

- time to rewrite the memo cards.

. time doctors

. the average duration of use of Antibioclic by doctors

We will take into account antibiotic dispensing based on the doctor's prescription and the monitoring of activity over a 12-month period. The costs will be calculated using Assurance Maladie tariffs.

This will be done by combining the results of the two previous stages. Given the 12-month time horizon, the costs will not be discounted. We will present the average costs per patient in each arm.

- 1. ***Efficiency data***

Effectiveness will be measured by the ratio between deliveries of defined daily doses (DDD) observed in the Assurance Maladie databases and the WHO defined daily doses between the different scenarios in the analysis [46-47].

We will look at defined daily doses (DDD) of all types of systemic antibiotics for all patients per 100 consultations [51]. To do this, we will stratify by specific antibiotic types (ie, tetracyclines, quinolones, β. lactamine/penicillin, other β. lactamine, other antibacterials, unspecified, etc.).

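### The only planned probability of cost-effectiveness is pairwise, against a comparator that names no arm, although the economic evaluation compares three strategies

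*Protocol*

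**What the plan says.** The secondary evaluation criteria (item 5) define the economic endpoint for three strategies: "Incremental cost-effectiveness ratio comparing the 3 alternatives: i) DAM visit with Antibioclic demonstration, ii) DAM visit without Antibioclic demonstration, iii) usual practice". Section 9 (Medico-economic study) follows this. It costs three strategies and adds: "Given that two strategies will be compared with current practice, it may be necessary to estimate several incremental cost-effectiveness ratios (ICERs"). It also plans a dominance analysis, in which a dominated intervention is one that costs more and achieves less than another.

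The statistics section (secondary endpoints, item 5) describes the outputs differently. Resources, mean costs and efficiency are to be given for each arm, but then "A table will show the difference between the two groups in terms of costs and effectiveness". The item closes with the only statement in the protocol on the probability of cost-effectiveness: "the probability that the use of antibioclic associated with a specific DAM visit is cost-effective compared with" "a standard DAM visit". This "will be calculated for different values of willingness to pay for a reduction in antibiotics"; no values are given.

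**The concern.** A payer choosing between three mutually exclusive options needs to know which is best at a given willingness to pay, and how sure one can be of that. A single pairwise probability answers this only in part, and here it is unclear which pair is meant. Two analysts could both follow the protocol and report different comparisons, and the choice is still open when the data arrive. Under either choice one strategy has no place in the probability statement. The sponsor presents the intervention as replicable nationally and takes the health insurer's perspective, so this output may be used for a funding decision.

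**Working it through.** **1. Which arm is the standard visit?** No protocol figure is at stake here, so the check starts from the wording.

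| Place in the protocol | Wording | Points to |
|---|---|---|
| Rationale, aim of the research | antibiotic-themed intervention described as "combining a usual visit (with awareness-raising on antibiotic resistance, work on preconceived ideas, feedback on practices") | arm 2 |
| 4.1.1 Main objective; section 9, objective | the same visit called *routine*, then *regular* | arm 2 |
| 4.1.1 and description of arm 3 | arm 3 is *usual practice* and also receives a delegate visit, on another theme | arm 3 |
| Inclusions and follow-up period | arm 3 receives no *specific* intervention on antibiotic prescribing, so *specific* against *standard* could mean arm 1 against arm 3 | arm 3 |

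Both readings have support in the text, and neither is settled.

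**2. Standard visit = arm 3.** The documents give no costs or willingness to pay, so all costs and effects below are assumptions, per doctor and against arm 3. Costs are taken as net of any saving on antibiotics.

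- Arm 2: 100 EUR more, 400 DDD avoided. Ratio to arm 3: 100/400 = 0.25 EUR per DDD.
- Arm 1: 300 EUR more, 450 DDD avoided. Ratio to arm 3: 300/450 = 0.67 EUR per DDD.
- Arm 1 against arm 2: (300 − 100)/(450 − 400) = 4.00 EUR per DDD.

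Net benefit is λ × DDD avoided − cost, where λ is the willingness to pay. At λ = 2 EUR, arm 1 gives 2 × 450 − 300 = 600, arm 2 gives 2 × 400 − 100 = 700, and arm 3 gives 0. For any λ between 0.67 and 4.00, arm 1 beats arm 3 but arm 2 is best. Strict dominance flags nothing, because arm 1 is both dearer and more effective.

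**3. Size of the probabilities.** From the sample-size section: SD 5,360, 2,400 doctors (800 per arm), 1.9 doctors per practice and ICC 0.05.

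- Design effect: 1 + 0.9 × 0.05 = 1.045.
- Standard error of a difference between two arms: 5,360 × √(2 × 1.045/800) ≈ 274 DDD, so 274 × λ on the net-benefit scale.

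Effects are treated as normal and costs as fixed. At λ = 0.5 in case 1 below, arm 1 against arm 3 gives (0.5 × 700 − 150)/137 = 1.46, a probability of 0.93. Arm 1 against arm 2 gives −100/137 = −0.73, a probability of 0.23. A simulation with 400,000 draws agrees and adds the three-way result. Ranges run from λ = 0.5 to λ = 5.

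| Assumed case (DDD avoided; extra cost) | P(arm 1 better than arm 3) | P(arm 1 better than arm 2) | P(arm 2 best of three) |
|---|---|---|---|
| 1: arm 1 700; 150. Arm 2 700; 50 | 0.93 to 0.99 | 0.23 to 0.47 | 0.76 to 0.53 |
| 2: arm 1 600; 150. Arm 2 800; 100 | 0.86 to 0.98 | 0.14 to 0.22 | 0.86 to 0.78 |

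Arm 2 is truly the best choice in both cases. In case 2 arm 1 is truly dominated, so the planned dominance check could pick it up. In case 1 the true effects are equal. By symmetry, and with costs fixed, arm 1 would look less effective than arm 2 in only about half of trials, so strict dominance would often not flag it.

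**4. Standard visit = arm 2.** The probability then addresses the added value of the demonstration directly and does not mislead as in step 2. It says nothing about arm 3: arm 1 can have a higher net benefit than arm 2 while both are below zero against usual practice.

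**The case against.** The strongest reply is that section 9 is already a three-strategy plan and that item 5 of the statistics section refers to it. Ratios are planned with 95% confidence intervals from a non-parametric bootstrap, costs and effects are reported per arm, and dominance is checked. In the example above, a per-arm table would show 300 EUR and 450 DDD beside 100 EUR and 400 DDD, and a reader could work out the 4.00 EUR increment. The details of a joint probability are also often left to an analysis plan, which is not at hand.

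Much of this stands, and it rules out three stronger readings that a reader might infer:

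- *The plan will favour arm 1 when arm 2 is better.* This can follow only if the comparator is arm 3. If it is arm 2, the planned probability is the comparison needed for that choice.
- *The probability is restricted to two groups.* That phrase describes the difference table, which is a separate item.
- *Only point estimates and dominance are planned across strategies.* The bootstrap intervals and per-arm results show otherwise.

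The reply does not remove the rest. Section 9 says only that several ratios may be necessary, and frames them as two strategies against current practice, so a ratio of arm 1 to arm 2 is not assured. Separate intervals around ratios do not give the probability that each arm is the best of three. And the protocol does not leave the probability open for a later plan: it specifies one pair and labels one member of it unclearly.

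**Conclusion.** The point holds in a limited form. The one planned probability of cost-effectiveness has a comparator that can be read as arm 2 or arm 3, the difference table refers to two groups in a three-strategy evaluation, and no output gives decision uncertainty across the three arms. If the comparator is arm 3, the probability for arm 1 can be about 0.86 to 0.99 although arm 2 has the higher net benefit. Those figures rest on assumed effects, costs and willingness to pay. They show that the problem can arise, not that it is likely. If the comparator is arm 2, the gap is that usual practice is left out. Severity is minor to moderate: this is the fifth secondary endpoint, the primary comparison is untouched, and the other planned outputs limit the harm.

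**What to change.** In the statistics section, secondary endpoints, item 5:

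1. Replace the two-group table with one for all three arms, ordered by cost. Give incremental costs, effects and ratios between successive non-dominated arms, and check extended as well as strict dominance. This makes explicit whichever increments bear on the decision, including arm 1 against arm 2 where neither is ruled out.
2. Replace the pairwise probability with, for each willingness-to-pay value, the probability that each of arms 1, 2 and 3 has the highest net benefit. Take it from one bootstrap that resamples practices within arm, since practices are the randomised unit.
3. If a pairwise probability is kept as a supplement, name both arms by number.

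The cost is a change of wording and a few lines of code on top of a bootstrap already planned. No new outcome or cost data are needed. The analysis file must carry a coded practice identifier, which the health insurer can supply because it randomises the places of practice.

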The proposed intervention is replicable on a national scale and could serve as a model for the future.

The method chosen for data collection, based on collaboration with health insurance departments and extraction of data from the SNDS, will help to limit missing data.

1. **DESCRIPTION OF EXPECTED BENEFITS**

The aim of the study is to identify the most effective ways of reducing the volume of antibiotics dispensed, with immediate benefits for public health:

. limiting the development of bacterial resistance,

. optimising antibiotic prescriptions (better quality prescriptions),

. lower costs.

The results will provide original information, at the end of a randomised comparative study, on the specific impact of 2 complementary types of intervention:

1. the use of visits by health insurance delegates,

2. demonstration of the use of the Antibioclic site.

Secondary analyses will enable us to better characterise the differentiated impact of the intervention according to prescribers or patient characteristics.

The study will provide an opportunity to raise GPs' awareness of the problem of antibiotic resistance on a large scale, and will raise awareness of :

. more than 800 doctors included in arm 1, who will receive awareness training from the Health Insurance delegate, feedback on their practices, and a demonstration of how to use the Antibioclic website,

. more than 800 doctors included in arm 2, who will benefit from awareness-raising by the Health Insurance Delegate and feedback on their practices.

The medico-economic study will document the potential impact on healthcare expenditure.

One of the ancillary benefits of the study will be to mobilise the partners around a joint project, on a theme that is of daily interest to primary care professionals.

1. **OBJECTIVES AND ASSESSMENT CRITERIA**
   1. ***OBJECTIVE AND MAIN EVALUATION CRITERIA***

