**Initial collection**

The Assurance Maladie will be responsible for extracting the data specific to the research and for building up the database.

The data collected will be data characterising GPs: age group (in 5-year increments from the age of 25), sex, classification of the commune of practice (according to INSEE urban area zoning, "major centres" (codes 111, 112, 120), "small centres" (codes 211, 212, 221, 222), "isolated towns" (code 400), and "other communes" (code 300) [46]), activity in terms of number of annual consultations, number of patients in the GP patient base, mode of practice (alone, in a group).

The Assurance Maladie randomises the GPs' places of practice and adds the allocated randomisation arm to the list of participating GPs, according to their place of practice.

The Assurance Maladie extracts data on antibiotic therapy prescriptions from all GPs included in the study (data for the 12 months preceding the visit) for descriptive purposes (T0).

**A 2nd round of** data **collection** will take place at the end of 12 months' follow-up: the French National Health Insurance will extract data on the dispensing of antibiotics prescribed by all GPs included in the study.

The data collection period will begin on the day of the DAM's visit.

- - 1. ***PARTICIPANT IDENTIFICATION***

The data will be centralised by the Assurance Maladie. No nominative data will be exported outside the databases of the Sickness Insurance departments.

The variables were selected after a pilot study, and the health insurance authorities paid close attention to CNIL regulations, to ensure that no data was directly identifiable (which is why the ages of practitioners are grouped into 5-year classes, and the communes classified by type).

- 1. ***Statistics***
     1. ***DESCRIPTION OF PLANNED STATISTICAL METHODS, INCLUDING TIMETABLE FOR INTERIM ANALYSES***

The analyses will be carried out using R 3.6.0 software.

The data will be described by the numbers and percentages of each modality for the qualitative variables and by the minimum, maximum, quartile, mean and standard deviation for the quantitative variables, overall and according to the 3 randomisation arms.

A hierarchical procedure will be used to successively test the comparison between the 3 arms, while maintaining a 5% alpha risk. The first hypothesis tested will be the difference between arm 1 and arm 3. If the test is significant, a second test will be performed comparing arm 1 to arm 2.

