For doctors who have not been visited by the DAMs, the start date of the data collection period will be allocated by drawing lots, and staggered over the 3 months (start date based on the visit dates available for the 3 randomisation arms).

- 1. ***Randomisation***

The Assurance Maladie will generate a list of GP practices that meet the inclusion criteria. It will then randomise the GP practices on a 1:1:1 basis. Doctors will be assigned to the randomisation arm to which their practice has been allocated.

1. **SAFETY / UNDESIRABLE EFFECT**

In the regulatory sense and within the meaning of the Jardé Law, this study does not constitute research involving human subjects. In the regulatory sense and within the meaning of the Jardé Law, this protocol does not involve any change in the usual management of patients, so any adverse events or effects observed will be unrelated to the study.

1. **MEDICO-ECONOMIC STUDY**

This section presents the objectives and methodology of the efficiency analysis, based on a cost-effectiveness analysis. The economic evaluation methodology follows the 2011 recommendations of the French National Authority for Health [49].

- 1. ***Objective, perspective and time horizon of the cost-effectiveness analysis***

The study involves a cost-effectiveness analysis comparing the delivery of antibiotics over a 12-month period in current practice, compared with two alternative strategies

i) an intervention carried out by the Délégués d'Assurance Maladie (Health Insurance Representatives) in general practices, combining a regular visit (with awareness-raising on antibiotic resistance, work on preconceived ideas, feedback on practices) and a demonstration of the use of Antibioclic,

1. an intervention carried out in the same way by the Délégués d'Assurance Maladie, but without Antibioclic being demonstrated.

This analysis will be carried out from the point of view of the Assurance Maladie Obligatoire over a 12-month period.

Costs will be estimated on the basis of information retrieved from the SNDS databases extracted by the Assurance Maladie in Pays de la Loire. The resources consumed will be valued at Assurance Maladie prices for drugs.

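### The stated 80% power at 450 DDD holds for neither step of the testing hierarchy: one test has about 38%, and the conditional arm 1 v arm 2 test can have less

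*Protocol*

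**What the plan says.** The statistical justification for the number of inclusions (protocol, section 7.2) gives these inputs: "the number of eligible doctors was estimated at 2,400 GPs who saw more than 100 different patients in 2018"; a mean of 7,671 DDD per doctor (SD 5,360) for that year; 1.9 GPs per practice; and an intra-class correlation of 0.05. At 5% alpha and 80% power it concludes that "we can then demonstrate a significant difference if we have at least an average difference of 450 DDD per doctor". The sentence refers to the compared arms in general. It does not mention the order of testing or give separate differences for the two comparisons.

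The description of planned statistical methods, in the same section, sets a hierarchy. Arm 1 v arm 3 is tested first, then: "If the test is significant, a second test will be performed comparing arm 1 to arm 2". The primary endpoint is compared by Student's t test.

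On arm size, the randomisation paragraph says "It will then randomise the GP practices on a 1:1:1 basis", and the description of expected benefits anticipates "more than 800 doctors included in arm 1" and the same for arm 2. The section on originality says the design will support a conclusion "on the specific added value of demonstrating the use of Antibioclic". In the hierarchy, that question rests on arm 1 v arm 2 alone.

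**The concern.** One power and one difference are made to serve two tests that do not have the same chance of success. The second test takes place only if the first is significant, so a conclusion on arm 1 v arm 2 requires both to succeed. Its probability cannot exceed the power of the arm 1 v arm 2 test alone. The single-test figure must also be checked, because if 450 DDD does not follow from the printed inputs, the claim fails at the first step as well.

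At stake is how the trial's sensitivity is understood, above all for the Antibioclic demonstration. Someone relying on the sample-size paragraph would think each comparison had an 80% chance of detecting 450 DDD, about 6% of the 2018 mean (450 / 7,671 = 5.9%).

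**Working it through.** **Inputs.** From the protocol: SD 5,360; 2,400 doctors in three arms, so about 800 per arm; 1.9 doctors per practice; ICC 0.05; alpha 5%; power 80%; unadjusted t test. Assumed: two-sided alpha (the protocol does not say), equal arms, equal practice sizes, normal approximation.

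**1. The plan's own figure.**
- Design effect = 1 + (1.9 − 1) × 0.05 = 1.045.
- Standard error of a difference = 5,360 × √(2 × 1.045 / 800) = 274.0 DDD.
- Difference with 80% power = (1.960 + 0.842) × 274.0 = about 768 DDD, not 450.
- Power at 450 DDD: 450 / 274.0 = 1.643, and Φ(1.643 − 1.960) = 0.375, about 38%.

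Other readings of the inputs do not recover 450 with about 800 per arm:

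| Variant | Difference with 80% power (DDD) | Power at 450 |
|---|---|---|
| 800 per arm, two-sided, design effect | 768 | 38% |
| 800 per arm, two-sided, no design effect | 751 | 39% |
| 800 per arm, one-sided, design effect | 681 | 50% |
| Arms 1 and 2 pooled, 1,600 v 800, two-sided, design effect | 665 | 47% |
| 2,400 in each arm, two-sided, design effect | 443 | 81% |

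For 80% power at 450 DDD, each arm would need about 2,228 × 1.045 = 2,328 doctors, or about 6,985 in all.

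**2. The second step.** With equal arms, the two test statistics share arm 1 and have correlation 0.5. Write d13 and d12 for the true differences. The power to conclude on arm 1 v arm 2 is the bivariate normal probability that both statistics exceed 1.960, with means d13 / 274.0 and d12 / 274.0:

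| d13 (DDD) | d12 (DDD) | Arm 1 v 3 alone | Arm 1 v 2 alone | Both significant |
|---|---|---|---|---|
| 450 | 450 | 38% | 38% | 22% |
| 600 | 450 | 59% | 38% | 30% |
| 900 | 450 | 91% | 38% | 37% |
| 768 | 768 | 80% | 80% | 69% |
| 1,152 | 768 | 99% | 80% | 80% |
| 857 | 857 | 88% | 88% | 80% |

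Equal differences mean that arm 2 does no better than arm 3. For 80% on both tests in that case, the standardised difference must be 3.128, and 3.128 × 274.0 = 857 DDD.

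**3. How much is due to the ordering.** At the difference where a single test truly has 80% power, the ordering costs at most about 11 points (80% to 69%), provided arm 2 is no worse than arm 3. At 450 DDD in both comparisons it costs about 16 points (38% to 22%). The larger part of the shortfall from 80% there, about 42 points (80% to 38%), comes from the single-test figure.

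**4. Granting the plan's premise.** If each test really had 80% power at 450 DDD, the standard error would be 450 / 2.802 = 160.6. With d12 at 450, the power for arm 1 v arm 2 would be 69%, 77%, 79% and 80% for d13 of 450, 550, 600 and 675 DDD. So even on its own terms the single figure does not cover the second test when arm 2 adds little over arm 3.

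**The case against.** Quoting power per comparison is common in a fixed-sequence procedure, and the paragraph does not claim joint power. It omits the ordering but does not misdescribe it. If the arm 2 visit works, as the rationale hopes, arm 1 v arm 3 is the larger difference and the ordering costs little. All of this is fair. It makes the ordering the smaller problem and confines its cost mainly to the case where arm 2 has little effect. It does not rescue the per-comparison figure, which is about 38% rather than 80%.

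A covariate-adjusted analysis could reach 450 DDD with 800 per arm if the residual SD were near 3,143, that is, if covariates explained about 66% of the variance (1 − (450 / 768)² = 0.66). The protocol plans an unadjusted t test, and section 7.1 collects the preceding 12 months' prescribing data for description.

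Four stronger readings are tempting but not supported:
- A reader might infer that 80% is right for a stand-alone test and that only the ordering spoils it. The printed inputs contradict that.
- If 450 DDD is taken as the arm 1 v arm 3 effect and arm 2 is assumed to deliver 25%, 50% or 75% of it, power for arm 1 v arm 2 falls to 50%, 27% or 10%, even granting the plan's standard error. Without the ordering it would be 56%, 29% and 10%. Nearly all of that fall comes from the smaller difference, and the protocol claims nothing below 450 DDD.
- A reader might infer that a non-significant or unperformed second test will be reported as no added value. No section says so, and how to read that result can be left to the analysis plan.
- The 443 DDD obtained with 2,400 doctors in each arm suggests that the total was used as the arm size. The protocol does not show its calculation, so this remains an inference.

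**Conclusion.** The point holds. The 80% power at 450 DDD is not delivered for either step. For arm 1 v arm 3, power at 450 is about 38%, and 80% is reached at about 768 DDD, or 10% of the 2018 mean (768 / 7,671). For arm 1 v arm 2, the power to conclude depends on both differences: about 22% at 450 and 450, 69% at 768 and 768, and about 80% at 1,152 and 768. If arm 2 equals arm 3, 80% needs about 857 DDD.

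These figures rest on two-sided 5% tests, equal arms of 800 and equal practice sizes. Variation in practice size would raise the design effect and lower power further. A one-sided test would raise single-test power at 450 only to about 50%. The error lies in the stated power. The order of testing itself is sound.

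**What to change.** In the statistical justification for the number of inclusions:

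1. Replace 450 DDD with the difference that follows from the printed inputs, about 768 DDD, and state the arm size, design effect and sidedness used.
2. Attach the 80% to arm 1 v arm 3 only.
3. For arm 1 v arm 2, give the probability that both tests are significant, for a stated pair of differences. For example: 69% if both are 768 DDD, and about 80% if arm 1 v arm 3 is 1,152 and arm 1 v arm 2 is 768.

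The cost is a rewritten paragraph and a short calculation. The trial already takes every eligible GP in the region, so enrolment is unchanged, as is the order of testing. The downside is a less favourable stated power, most of all for the Antibioclic comparison.
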